## Abstract

**Background:**

Powered ankle-foot prosthetic devices can generate net positive mechanical work during gait, which mimics the physiological ankle. However, gait deviations can persist in individuals with transfemoral limb loss because of habit or lack of rehabilitation. Prosthetic research efforts favor the design or evaluation of prosthetic componentry and rarely incorporate any type of rehabilitation, despite evidence suggesting that it is critical for minimizing gait imbalances. Given the accelerated rate of innovation in prosthetics, there is a fundamental knowledge gap concerning how individuals with transfemoral limb loss should learn to correctly use powered ankle-foot devices for maximum functional benefit. Because of the recent advances in prosthetic technology, there is also a critical unmet need to develop guidelines for the prescription of advanced prosthetic devices that incorporate both physical and psychological components to identify appropriate candidates for advanced technology.

**Objective:**

The primary goal of this investigation is to examine the roles of advanced prosthetic technology and a device-specific rehabilitative intervention on gait biomechanics, functional efficacy, and pain in individuals with transfemoral limb loss. The secondary goal is to develop preliminary rehabilitation guidelines for advanced lower limb prosthetic devices to minimize gait imbalances and maximize function and to establish preliminary guidelines for powered ankle-foot prosthetic prescription.

**Methods:**

This prospective, multisite study will enroll 30 individuals with unilateral transfemoral limb loss. At baseline, participants will undergo a full gait analysis and assessment of function, neurocognition, cognitive load, subjective preferences, and pain using their current passive prosthesis. The participants will then be fitted with a powered ankle-foot device and randomized into 2 equal groups: a powered device with a device-specific rehabilitation intervention (group A) or a powered device with the current standard of practice (group B). Group A will undergo 4 weeks of device-specific rehabilitation. Group B will receive the current standard of practice, which includes basic device education but no further device-specific rehabilitation. Data collection procedures will then be repeated after 4 weeks and 8 weeks of powered ankle use.

**Results:**

This study was funded in September 2017. Enrollment began in September 2018. Data collection will conclude by March 2024. The initial dissemination of results is expected in August 2024.

**Conclusions:**

The projected trends indicate that the number of individuals with limb loss will dramatically increase in the United States. The absence of effective, evidence-based interventions may make individuals with transfemoral limb loss more susceptible to increased secondary physical conditions and degenerative changes. With this expected growth, considerable resources will be required for prosthetic and rehabilitation services. Identifying potential mechanisms for correcting gait asymmetries, either through advanced prosthetic technology or rehabilitative interventions, can provide a benchmark for understanding the optimal treatment strategies for individuals with transfemoral limb loss.

**Trial Registration:**

ClinicalTrials.gov NCT03625921; https://clinicaltrials.gov/study/NCT03625921

**International Registered Report Identifier (IRRID):**

DERR1-10.2196/53412

## Introduction

### Background

There are approximately 1.9 million Americans with limb loss today, with an estimated 185,000 people who undergo an amputation procedure each year [1]. Over the last 2 decades, the Department of Veterans Affairs (VA) and the Department of Defense (DoD) have experienced an increase in the number of veterans and service members with lower limb loss [2]. Since the start of the most recent conflicts, more than 1700 service members have experienced combat-related limb loss, with the vast majority of these traumatic amputations of the lower limb [2-4]. VA, the largest integrated health care network in the United States, serves this unique population after their separation from active duty and provides care for an additional 41,000 veterans with lower limb loss [5]. Transfemoral limb loss, the second most common level of lower limb loss, accounts for one-fifth of the total limb loss population in the United States [6]. With this already large population expected to grow, effective outcomes-based clinical practice will be necessary to improve mobility, decrease long-term disability, and provide a higher quality of life.

### Abnormal Gait Mechanics for Individuals With Transfemoral Limb Loss

Individuals with transfemoral limb loss have unique functional challenges owing to the loss of the knee and ankle joints [7-9]. Gait mechanics of individuals with transfemoral limb loss have been extensively investigated, with abnormalities typically characterized by asymmetries in stance phase biomechanics [10-13]. Individuals with transfemoral limb loss exhibit increased ipsilateral hip extensor activity and hip power, which is thought to be compensation for the lack of ankle power normally provided by the gastroc-soleus complex [14]. Consequently, compensatory mechanisms at joints proximal to the level of limb loss are often used to replace the function normally delivered by the muscles surrounding the ankle joint [12]. Individuals with unilateral transfemoral limb loss also tend to walk with longer stance times on the intact versus prosthetic limb [10], which can lead to a corresponding asymmetrical load distribution [15]. These asymmetrical joint forces place greater demands on the intact limb, which may explain the higher prevalence of musculoskeletal injuries, pain, and joint degeneration of the intact limb compared with uninjured individuals [16,17]. Significant among these secondary conditions is pain, specifically in the intact knee and lower back. In a study of experienced prosthesis users, knee pain in the intact limb was the primary complaint of 75% of individuals with transfemoral limb loss [18]. In a sample of 63 male veterans with traumatic lower limb loss, individuals with transfemoral limb loss were 5 times more likely to have intact knee pain compared with neurotypical participants [16]. Among individuals with lower limb loss (both transtibial and transfemoral), 71% reported back pain within the previous month, but individuals with transfemoral versus transtibial limb loss were significantly more likely to have greater pain intensity [19]. Chronic, persistent pain can lead to limitations in function. There is a significant need to explore the effects of advanced prosthetic technologies and rehabilitative interventions on pain reduction, function, and biomechanics.

### Biomimetic Prosthetic Technology

New technologies in lower limb prostheses have attempted to combat gait pathologies by generating biomimetic ankle power through spring-clutch mechanisms or advanced sensor and actuator technology [20]. Recent advances in microelectronics, battery technologies, and the development of several new types of actuators [21,22] have ushered in the development of powered lower limb prostheses that can better replicate the positive work phases of the ankle through the use of actuators, motors, or pneumatic muscles [23-27].

The Empower (Ottobock Inc), which uses a series-elastic actuator and a carbon-composite footplate, is currently the only commercially available powered ankle-foot device [28,29]. The Empower has been investigated in the population of individuals with transtibial limb loss, but it has yet to be fully investigated in individuals with transfemoral limb loss [30-33]. In a study of individuals with transtibial limb loss, the use of a powered versus passive ankle-foot device reduced the peak resultant force and knee adduction moment on the unaffected leg during level ground walking, potentially limiting the risk of secondary musculoskeletal comorbidities [31]. Individuals with transtibial limb loss using the same powered ankle-foot device had improved ankle power, greater net trailing limb step-to-step transition work, and a lower metabolic rate compared with a passive energy storing and returning ankle-foot prosthesis during level ground ambulation [32].

Although biomimetic prosthetic devices can better approximate biological ankle biomechanics, residual gait deviations can persist, either because of habit or a lack of proper rehabilitative training. For example, despite greater ankle power generation with powered ankle-foot device use, individuals with transtibial limb loss can still walk with compensatory strategies at the proximal joints, which can be attributed to the introduction of new interlimb asymmetries from the uniarticular function of the device [30]. Therefore, device-specific rehabilitation may be needed to minimize or correct the reported deficiencies. Similarly, in the absence of an evidence-based rehabilitation program to correct or minimize preexisting gait asymmetries, instrumented gait analyses that assess the biomechanical function of prosthetic devices may be more likely to quantify the physical gait deviations developed through habit or lack of training rather than device-specific attributes [34]. Therefore, it may be more accurate to postulate that powered ankle-foot devices, through the generation of normative ankle power during push off, offer an opportunity to minimize gait deviations and normalize prosthetic function but not without the incorporation of a rehabilitation program to train prosthesis users to reduce existing gait deviations.

### Prosthetic Rehabilitation Programs

The current state of prosthetic research efforts appears to favor the design and evaluation of prosthetic componentry, particularly with respect to gait mechanics, and rarely incorporates or reports any type of physical therapy (PT) program or device-specific training [34]. Given the accelerated rate of technological innovation in prosthetic devices, there is a fundamental knowledge gap concerning how individuals with lower limb loss should learn to correctly use this advanced, powered technology for maximum benefit. However, previous investigations have examined the effectiveness of rehabilitation protocols on the outcomes of individuals with transfemoral limb loss who used passive prosthetic devices. Prosthetic gait training based on proprioceptive feedback for individuals with transfemoral limb loss was more effective for improved weight-bearing and temporal-spatial parameters than traditional gait training [35]. Sjodahl et al [36] used instrumented gait analysis to measure the gait parameters of individuals with unilateral transfemoral limb loss before and after a training program and reported improved walking speed and sagittal plane hip kinematic symmetry after training. However, the authors also reported increases in compensatory strategies for the intact limb, including an increase in the intact knee extension moment. Virtual reality–based gait training with real-time biomechanical feedback improved frontal plane hip, pelvis, and trunk motion during level ground walking [37]. Currently, there have been no published studies detailing the effects of a device-specific rehabilitation program on the biomechanical or functional outcomes of individuals with transfemoral limb loss who use a powered ankle-foot prosthesis. In this investigation, this knowledge gap will be addressed, and a benchmark to understand optimal treatment strategies will be provided for individuals with transfemoral limb loss to minimize gait impairments.

### Summary

The development of evidence-based health care practices is critical to maximizing prosthetic and health outcomes in the growing population of individuals with transfemoral limb loss. Identifying potential mechanisms for correcting gait asymmetries, through advanced prosthetic technology, rehabilitative interventions, or both, can provide a benchmark to better understand the optimal treatment strategies for individuals with transfemoral limb loss. Despite research suggesting that an evidence-based rehabilitation program that incorporates prosthetic gait training is a critical factor in minimizing compensatory mechanisms [38-40], most prosthetic device protocols fail to incorporate any type of significant rehabilitation or device-specific training. Therefore, this investigation will be the first to elucidate the effects of an advanced powered prosthesis and the role of rehabilitative interventions on gait biomechanics, performance, and pain in individuals with transfemoral limb loss.

### Study Objectives

The overarching goal of this investigation is to examine the roles of advanced prosthetic technology and a device-specific rehabilitative intervention in individuals with transfemoral limb loss. The central hypothesis is that powered plantarflexion, coupled with an evidence-based, device-specific PT intervention, will improve biomechanical outcomes, which will correlate with decreased pain and improved functional performance. The objectives of this investigation are as follows:

To examine the biomechanical and functional efficacy of a powered prosthesis compared with a passive prosthesis for individuals with transfemoral limb lossTo determine the effects of a powered prosthetic ankle-foot device and a PT intervention on lower extremity kinematic and kinetic patterns, functional efficacy, and pain in individuals with transfemoral limb lossTo develop preliminary rehabilitation guidelines for a powered ankle-foot device to minimize gait imbalances and maximize function, as well as to establish preliminary guidelines for powered ankle-foot prosthetic prescription

## Methods

### Study Overview

This investigation will be a prospective, multisite study including VA New York Harbor Healthcare System (VANYHHS), James A. Haley Veterans’ Hospital (JAHVH), and Walter Reed National Military Medical Center (WRNMMC). Enrollment began in September 2018, and data collection is expected to conclude in 2024. Briefly, 30 individuals with transfemoral limb loss are expected to be enrolled equally across the 3 sites. For all participants, a full biomechanical gait analysis, functional measures, surveys, neurocognitive assessment, cognitive load assessment, and pain assessment will be captured at baseline with their clinically prescribed passive energy storing and returning ankle-foot prosthesis. The participants will be fitted with a powered ankle-foot device (Empower) and then be evaluated for safe use. The participants will then be randomly assigned into 2 groups: a powered ankle-foot device with a 4-week, 8-session device-specific PT intervention (group A) or a powered ankle-foot device with the current standard of practice (group B), which includes basic device education and training provided by the study prosthetist (outlined in the Powered Ankle-Foot Device Standard of Practice section), but no device-specific PT intervention. Group A will then undergo 4 weeks of device-specific rehabilitation, while group B will not receive any further PT. All participants will then undergo a full gait analysis as well as assessments of function, subjective preferences, neurocognition, cognitive load, and pain after 4 weeks and 8 weeks of powered ankle-foot device use (Figure 1). A comparison between the 2 groups will help evaluate the efficacy of a powered versus passive prosthesis, as well as elucidate the contribution of device-specific effects to rehabilitation-specific effects for individuals with transfemoral limb loss.

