### Participants

A convenience sample of 30 individuals with unilateral transfemoral limb loss will be recruited for this study (Textbox 1 shows the inclusion and exclusion criteria). All participants will consent to participate before participating in any study activities. The participants will be randomly stratified into 2 study arms: group A, a powered ankle-foot device with device-specific PT (15/30, 50%), and group B, a powered ankle-foot device with standard of practice (15/30, 50%), which includes basic device education and training but no device-specific PT intervention. Recruitment of participants will be on a first-come, first-serve basis among the patients of VANYHHS, JAHVH, and WRNMMC. The participants will be recruited through the VANYHHS, JAHVH, and WRNMMC rehabilitation and prosthetic clinics. All participants will have experience using a microprocessor knee and will currently use a passive-elastic ankle-foot prosthesis.

Inclusion and exclusion criteria.

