### Baseline Visit

#### Informed Consent, Enrollment, and Randomization

Informed consent for each potential participant will be conducted in person in a private room. The site-principal investigator or qualified designee will explain the study protocol in detail. The participants will be asked to consent to randomization of the treatment group, either to be fit with the powered ankle-foot device and receive device-specific PT (group A) or to be fit with the powered ankle-foot device and receive the current standard of practice that does not include device-specific PT (group B). The participants will be asked to make a commitment to be available for all study-related activities. The individuals will be given adequate time to review and comprehend all information about the study before agreeing to participate, minimizing the possibility of coercion and undue influence. After the study has been explained and consent has been given, the participants will be randomized into the 2 groups using a computer-generated algorithm that block randomizes participants into each group at each site.

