#### Baseline Data Capture

Regardless of the group assignment, all participants will undergo baseline data capture using their current passive energy storing and returning prosthesis. The study prosthetist will ensure proper fit and alignment of the prosthesis before any data collection. Once fit and alignment are confirmed, the participants will complete 3 surveys: an assessment of quality of life, the Prosthesis Evaluation Questionnaire (PEQ), and the PEQ Addendum. Then, pain, cognitive load, neurocognition, biomechanical gait analysis, and functional outcomes will be captured at baseline for all participants on their current passive energy storing and returning prosthesis.

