#### Functional Outcome Measures

The effects of the prosthetic devices and the rehabilitative intervention on physical performance will be evaluated using agility and mobility tests, including the 6-minute walk test (6MWT) [58], the Amputee Mobility Predictor with prosthesis (AMPpro) [59], and the Comprehensive High-Level Activity Mobility Predictor (CHAMP) [60]. By capturing the functional measures in each group, the effects of the ankle-foot device can be isolated from the rehabilitation effects on physical performance. These measures are as follows:

6MWT: the 6MWT measures the distance an individual can walk in 6 minutes without help or encouragement. It is a valid and reliable measure that correlates with physical function and has good interrater and intrarater reliability in individuals with lower limb loss [58].AMPpro: the AMPpro is a 21-item instrument designed to measure prosthetic mobility in individuals with lower limb loss [59].CHAMP: participants who attain a score of 37 or higher on the AMPpro will undergo the CHAMP, which consists of the following tasks:Single limb stance: participants fold their arms across their chest and then lift their foot above a 15-cm cone or box. The test ends when the foot touches the ground again (or until 30 s) or if the arms uncross. This procedure is performed on both feet.Edgren Sidestep Test: participants sidestep left and then right along a 5-meter line of cones (1 meter apart). The sidestep test lasts for 10 seconds.T-Test: the T-Test measures forward, lateral, and backward walking (or running) and sidestepping in a T pattern.Illinois Agility Test: this advanced agility test requires the participant to run or walk and change direction around multiple cones. Over 60 meters, participants perform 90° and 180° turns 11 times around multiple cones.

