#### Powered Ankle-Foot Prosthesis Fitting

Following all baseline data collection procedures, all participants will then be fit with the Empower. Study prosthetists at VANYHHS, WRNMMC, and JAHVH are highly experienced in fitting all commercial microprocessor knees and the Empower. The study prosthetists will bench align the powered ankle-foot device onto the participant’s existing microprocessor prosthetic knee and socket. Once the powered ankle-foot device is fitted and bench-aligned to the prosthetic knee and socket, dynamic alignment of the prosthetic knee and ankle will occur. Initially, the study prosthetist will ensure proper alignment of the microprocessor prosthetic knee with the Empower turned off. The Empower will still function (ie, articulate) with the power off but will not provide net positive plantarflexion torque. The microprocessor prosthetic knee software and prosthesis alignment will be adjusted during standing and walking tasks, as necessary, until the prosthetist and the participant are satisfied with the knee alignment. Once the microprocessor knee setup is completed, the Empower will be powered on and adjusted according to the manufacturer’s specifications. Briefly, the participants will sequentially walk at 3 different speeds (slow, self-selected, and fast) while the stiffness and power delivery of the powered ankle-foot device is tuned [33]. If further dynamic adjustments to prosthetic knee alignment are necessary, these adjustments will be made at this point.

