### Planned Statistical Analysis for Biomechanical and Functional Outcomes

Although there are numerous biomechanical and physiological parameters that can be evaluated following gait analysis [61], this investigation will focus on the biomechanical parameters that are most relevant, commonly used, able to discriminate, and have specific clinical relevance for individuals with transfemoral limb loss. The primary biomechanical outcome measures will include measures of rollover shape, individual characteristics of the 3D ground reaction force, and ankle, knee, and hip joint angles, moments, and powers (on both the intact and affected limbs). To evaluate the load distribution of the medial and lateral knee compartments, the peak resultant ground reaction force, ground reaction force rate, peak knee external adduction moments, and knee external adduction moment rate will be compared between the baseline (passive energy storing and returning condition) and the powered condition at each follow-up visit.

Linear mixed-effects models will be used to identify statistically significant differences in gait temporal-spatial and biomechanical variables for all walking speeds. The fixed effects will be the average differences in gait biomechanical and temporal-spatial variables by prosthetic ankle type (powered vs passive). These models also estimate random effects because of differences in mean biomechanical variables across participants, as well as the random effects associated with minimized variability, as the participants will be tested with both prostheses. For example, a linear mixed-effects regression will be used to examine the relationship between the intact knee peak external adduction moment and the prosthetic ankle-foot condition. Peak intact knee external adduction moment will be the dependent variable, whereas ankle-foot condition will be the independent variable, and participant-by-ankle-foot condition will be modeled as random effects. Pair-wise comparisons will be tested for significance using linear contrasts with a Tukey honestly significant difference or by applying a Bonferroni correction, where applicable. In addition, linear mixed-effects regression will be used to determine the association between prosthetic peak ankle power and foot condition.

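### Comparing the two groups estimates the added effect of physical therapy, not powered versus passive, and the gait model as stated mixes half of any therapy effect into the device contrast

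*Protocol article*

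**What the plan says.** The first study objective is to compare a powered with a passive prosthesis on biomechanics and function. The Study Overview links this to the randomised groups: "A comparison between the 2 groups will help evaluate the efficacy of a powered versus passive prosthesis". Functional Outcome Measures adds that, by measuring each group, "the effects of the ankle-foot device can be isolated from the rehabilitation effects on physical performance".

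The design sections describe the following:

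- **Passive device.** "Regardless of the group assignment, all participants will undergo baseline data capture using their current passive energy storing and returning prosthesis" (Baseline Data Capture). Participants return to it only after the last data collection (Data Collection Visit 3).
- **Powered device.** "Following all baseline data collection procedures, all participants will then be fit with the Empower" (Powered Ankle-Foot Prosthesis Fitting). All are assessed on it after 4 and 8 weeks.
- **Arms.** Group A has the powered device with device-specific PT. The other arm is "group B, a powered ankle-foot device with standard of practice" (Participants). Randomisation therefore assigns PT, not the device.

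Under Planned Statistical Analysis for Biomechanical and Functional Outcomes, the knee-loading measures are to be "compared between the baseline (passive energy storing and returning condition) and the powered condition at each follow-up visit". The fixed effects of the gait models are described as mean differences by ankle type. In the worked example, ankle-foot condition is the independent variable and participant-by-condition is random. No PT, group or visit term is named there. The section on cognitive outcomes does name PT as a fixed effect next to ankle type.

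**The concern.** Two statements about what the data can show do not fit the design.

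First, a comparison of two arms that both wear the powered device at every follow-up cannot inform powered versus passive.

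Second, the contrast that can inform it is a before-after change with the passive device always first. For the gait variables, the model as described averages that change over both arms, although group A's follow-up data come after about eight PT sessions and a home exercise programme.

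At stake is the estimate for the first objective. It could be reported as device efficacy when part of it is therapy and part may be time or repeat testing. The third objective is to draw preliminary prescription guidelines for the powered device, so the label matters.

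**Working it through.** The plan gives no figure for the device contrast, so there is none to reproduce. Table 5 reports power for the group-by-time interaction, which is the PT contrast.

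**Inputs.** 15 participants per arm (Power Analysis and Sample Size Estimation); passive at baseline only; powered at weeks 4 and 8 in both arms; PT in group A only. For a given outcome, let:

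- D = effect of the powered device;
- T = change due to time, practice, acclimation and device order;
- P = added effect of device-specific PT.

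**Change from baseline, by group**

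- Group A: D + T + P
- Group B: D + T

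**What each comparison estimates**

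1. Between groups: (D + T + P) − (D + T) = P. D cancels, whatever its size.
2. Ankle type as the only fixed effect, complete data: [15(D + T + P) + 15(D + T)] / 30 = D + T + P/2.
3. Group B's change: D + T.

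If weeks 4 and 8 are averaged, T and P become their averages over the two visits. The factor of one half is unchanged.

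**Numerical illustration.** T = 20 and P = 30 are assumed, in arbitrary units:

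| True D | Between groups | Ankle type only | Group B change |
|---|---|---|---|
| 0 | 30 | 35 | 20 |
| 30 | 30 | 65 | 50 |
| 60 | 30 | 95 | 80 |

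The between-group column does not move with D. The ankle-type column exceeds group B's change by P/2 = 15 in every row. Group B's change still exceeds D by T.

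**Scale for outcomes the gait model covers.** The size of P is unknown. If it is zero, the shift is zero. If P equalled the Table 5 difference, the shift would be 15/2 = 7.5 N/kg/s for ground reaction force rate and 1.1/2 = 0.55 N m/kg/s for knee adduction moment rate. This is conditional: Table 5 labels these values only as differences from preliminary analyses.

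**Precision.** With equal variance of change in the two arms, using 15 rather than 30 participants widens the interval by sqrt(30/15) = 1.41. This is an upper figure, because group A can still contribute to the common baseline mean and to the variance estimates.

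**The case against.** The best defence is that the gait section should not be read alone. The general Statistical Analysis section compares outcomes by device category and also by PT, and it mentions adjusting variables. The penalised pain regression includes ankle type and intervention. The cognitive model has both terms. The sample size rests on the group-by-time interaction. The Limitations section names covariates (age, time since limb loss, etiology, knee type) that the gait section omits, so that section's list of terms is not complete. A condensed article may leave full model terms to an analysis plan that is not shown.

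This shows that PT is meant to be examined. It does not put PT into the gait model, whose fixed effect and worked example are specific. Nor do the listed covariates help: they are constant within a participant, so as main effects they leave a balanced within-participant contrast unchanged.

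Other points stand in part:

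- The Study Overview only says that the comparison will help. But the comparison contains no D at all, so the softer verb does not make the statement right.
- A reader might infer that the isolation claim in Functional Outcome Measures is simply false. It is partly right: group B's change is free of device-specific PT, and the difference between groups gives the PT increment. It overstates only by leaving out T.
- A reader might halve the 60 m in Table 5 and report 30 m of spurious device effect on the 6-minute walk. The documents do not support this as a finding. The ankle-type model is stated for gait variables, and nothing shows that PT alone would yield the full 60 m.
- The before-after design is described openly, and the resulting guidelines are called preliminary.

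**Conclusion.** The Study Overview sentence is wrong as written: the group comparison identifies only the added effect of PT on top of the powered device. Powered versus passive is a fixed-order, uncontrolled, within-participant change. For the gait variables, the stated model would return device + time + half the PT effect. That factor of one half assumes equal arms, complete data and no PT term in the model. The absolute size cannot be given because P and T are unknown. The shift overstates the device effect if PT acts in the same direction as the device, and understates it if PT acts in the opposite direction.

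It would go too far to conclude that the trial's randomised comparison is damaged, or that group A must be discarded. Randomisation and the group-by-time test are unaffected, and a model with a suitable PT term can keep all 30 participants. Nor does any reanalysis remove T: no participant has a passive assessment after the powered one, and no arm stays on the passive device.

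**What to change.** 1. **Study Overview:** state that the comparison of groups A and B estimates the added effect of device-specific PT in people using the powered device.
2. **Gait model:** add group-by-visit terms. Take the device contrast as the change without PT, that is, group B from baseline to week 4 and to week 8, with group A kept in the model. A plain group main effect is not enough: it is constant over visits and leaves P/2 in the device term. The same care with coding applies to the PT term in the cognitive model.
3. **Reporting:** describe this contrast as an uncontrolled before-after change on switching to the powered device, still including time, practice and order effects. Qualify the isolation claim in Functional Outcome Measures in the same way.
4. **Limitations:** list the fixed device order and the absence of a concurrent or later passive assessment.

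No new data are needed. The cost is a device interval up to about 1.4 times wider. The change removes PT from the device estimate and labels the remaining confounding, but does not remove it.
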